## Abstract

**Background:**

After a cardiac event, a large majority of patients with cardiac conditions do not achieve recommended behavior change targets for secondary prevention. Mental health issues can also impact the ability to engage in health behavior change. There is a need for innovative, flexible, and theory-driven eHealth programs, which include evidence-based strategies to assist patients with cardiac conditions with their recovery, especially in behavioral and emotional self-management.

**Objective:**

The aim of this study is to determine the short- and longer-term behavioral and emotional well-being outcomes of the *Back on Track* web-based self-management program. In addition, this study will test whether there is enhanced benefit of providing one-on-one telephone support from a trained lifestyle counselor, over and above benefit obtained through completing the web-based program alone.

**Methods:**

People who have experienced a cardiac event in the previous 12 months and have access to the internet will be eligible for this study (N=120). Participants will be randomly assigned to one of the two study conditions: either “self-directed” completion of the *Back on Track* program (without assistance) or “supported” completion of the *Back on Track* program (additional 2 telephone sessions with a lifestyle counselor). All participants will have access to the web-based *Back on Track* program for 2 months. Telephone sessions with the supported arm participants will occur at approximately 2 and 6 weeks post enrollment. Measures will be assessed at baseline, and then 2 and 6 months later. Outcome measures assessed at all 3 timepoints include dietary intake, physical activity and sitting time, smoking status, anxiety and depression, stage of change, and self-efficacy in relation to behavioral and emotional self-management, quality of life, and self-rated health and well-being. A demographic questionnaire will be included at baseline only and program acceptability at 2 months only.

**Results:**

Recruitment began in May 2020 and concluded in August 2021. Data collection for the 6-month follow-up will be completed by February 2022, and data analysis and publication of results will be completed by June 2022. A total of 122 participants were enrolled in this study.

**Conclusions:**

The *Back on Track* trial will enable us to quantify the behavioral and emotional improvements obtained and maintained for patients with cardiac conditions and, in particular, to compare two modes of delivery: (1) fully self-directed delivery and (2) supported by a lifestyle counselor. We anticipate that the web-based *Back on Track* program will assist patients in their recovery and self-management after an acute event, and represents an effective, flexible, and easily accessible adjunct to center-based rehabilitation programs.

**Trial Registration:**

Australian New Zealand Clinical Trials Registry ACTRN12620000102976; http://www.anzctr.org.au/Trial/Registration/TrialReview.aspx?id=378920&isReview=true

**International Registered Report Identifier (IRRID):**

DERR1-10.2196/34534

## Introduction

### Background

Cardiovascular disease is the primary cause of death and disability, both globally [1] and in Australia [2]. With improvements in medical care, increasing numbers of people survive their first cardiac event; however, those who survive are at increased risk of a subsequent event and premature death [3]. The major focus of preventive cardiology is the recovery and rehabilitation of these survivors, with a view to reducing re-events and premature mortality [4].

Secondary prevention, including behavior modification and mood management, is essential for people who have experienced a cardiac event [5]. Up to 90% of the overall risk of acute myocardial infarction (AMI) is attributed to modifiable factors including, physical inactivity, poor diet, cigarette smoking, and medication nonadherence [6]. The survival benefits of increased physical activity, dietary change, and smoking cessation in patients with cardiac conditions have been demonstrated in numerous studies [7,8]. In addition, emotional well-being is essential for the overall health of those with cardiac conditions. Those who experience postevent mental health problems such as anxiety or depression have a poorer recovery than their nondistressed counterparts, with higher rates of hospital readmission [9], more re-events [10], and earlier mortality in the years following [11,12].

Unfortunately, despite the known benefits of behavior change, a large majority of cardiac event survivors do not achieve recommended targets for secondary prevention, with high rates of unhealthy diets, physical inactivity, and resumption of smoking in the postevent year [4,13,14]. Even among those who attend cardiac rehabilitation (CR) programs, initial lifestyle changes are rarely sustained [15]. Mental health problems, such as depressed mood [16] and cognitive barriers, such as negative thoughts [17], also decrease cardiac patients’ ability to undertake health-enhancing behavior change.

While CR is recommended for all cardiac event survivors after an acute event [18] and has been shown to improve health outcomes [19,20], center-based programs are underutilized with evident low participation rates [21,22]. In Australia, research has demonstrated that only approximately 30% of eligible people attend CR programs within 10 weeks of discharge [23]. Nonattendance is partly attributable to access difficulties, with travel time and distance from the venue, and limited car access being key barriers [24]. Regional and rural-based patients with cardiac conditions, as well as those who are younger and have returned to work, are particularly disadvantaged in terms of access to center-based support [25].

Up to 50% of cardiac event survivors have expressed the desire for flexible alternatives to center-based programs, many preferring home-based options, including eHealth [26]. Systematic reviews of telehealth interventions for people with coronary heart disease (CHD), including both telephone- and internet-based interventions, indicate that these programs provide effective risk factor reduction and secondary prevention [27,28]. Research on the effectiveness of web-based support for people with CHD has demonstrated improvements in behavioral and physiological indicators [29-31]. Emerging evidence suggests that outcomes can be enhanced by the addition of concurrent one-on-one telephone support from a health professional [32]. Current estimates suggest that almost 90% of Australian adults are active internet users [33] and that approximately 50% of users, including those of older ages, access health-related information [34], highlighting the potential for the use of web-based health programs with this population.

To our knowledge, there are no programs that aim to equip people with CHD with cognitive and behavioral skills to maintain psychosocial and behavioral health in the long term. People need evidence-based strategies and tools to develop skills to self-manage their health in the longer term [15]. Research has consistently highlighted the importance of theory-driven programs in assisting people with behavior change [35]. For example, self-regulation theory, defined as a goal guidance process aimed at the attainment and maintenance of personal goals [36], underpins several behavioral interventions to support change, such as self-monitoring, feedback, reward, and goal-setting [37,38]. Likewise, cognitive-behavioral therapy (CBT) has been used successfully to assist people with CHD in self-management of both behavioral [39] and psychosocial [40] risk factors. Motivational interviewing (MI) has also been shown to improve engagement and to decrease resistance [41], and it can enhance CR outcomes [42]. For cardiac patients, self-efficacy of behavior change has been shown to be associated with short- and longer-term maintenance of exercise and smoking cessation [43,44]. Evidence suggests that outcomes are optimal when these theories, interventions, and strategies are integrated [45,46].

With the aim of addressing gaps in secondary preventive care for people with CHD, the Australian Centre for Heart Health (ACHH) developed a face-to-face, group-based self-management program, *Beating Heart Problems,* which was underpinned by a framework of self-regulation theory and patient-centered care. Based on the principles and strategies of CBT and MI, the program was designed to provide cardiac event survivors with the cognitive and behavioral skills to self-manage their mood and health behaviors in the long term. A randomized controlled trial (RCT) of the *Beating Heart Problems* program, involving 275 cardiac event survivors, demonstrated that the intervention group showed a superior reduction in 2-year risk of a recurrent event, greater improvements in functional capacity and behavioral health, and greater reductions in depression incidence and severity, compared to the control group [47,48]. To overcome issues of access, accessibility, and inequities, the face-to-face program was translated for web-based delivery. The web-based program, titled *Back on Track*, is underpinned by the same frameworks and theories as the face-to-face program and includes modules that focus on both behavioral and emotional aspects of recovery. In a pilot study, the web-based *Back on Track* program was shown to be acceptable and useful in terms of self-management support following a cardiac event [49].

### Objectives

The aim of this study is to assess the benefits, in terms of behavioral and emotional well-being, of the web-based *Back on Track* self-management program, and to test whether participants obtain enhanced benefit through the provision of one-on-one telephone support from a trained lifestyle counselor (supported arm), over and above benefit obtained through completing the web-based program alone (self-directed arm). By including 2 follow-up assessments, one on postprogram completion (2 months) and one at 4 months post program (6 months postenrollment), we aim to assess both immediate and sustained benefits.

We hypothesize that participants randomly allocated to each arm of the trial will show significant improvement in their behavioral and emotional well-being, self-efficacy, and self-rated health from the preprogram to postprogram assessments, with benefits sustained 4 months after program completion. We also hypothesize that participants allocated to the supported program will demonstrate superior improvements in behavioral and emotional well-being, self-efficacy, and self-rated health compared to those allocated to the self-directed arm, at both the postprogram and follow-up assessments.

Ethical approval was granted by the Deakin University Human Research Ethics Committee (2019-438). This project has been funded by the HCF Research Foundation. This study will be conducted and reported in accordance with the CONSORT-EHEALTH guidelines [50].

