## Methods

### Study Design

This project uses a 2-armed RCT design, with participants who register to be involved in the trial being randomly allocated to one of two arms: either “self-directed” completion of the *Back on Track* program or “supported” completion of the *Back on Track* program. The self-directed arm involves participants completing the web-based *Back on Track* program at their own pace without assistance. The supported arm involves the addition of 2 telephone sessions with a trained lifestyle counselor. The telephone sessions are protocol driven, with a written manual developed by a health psychologist.

Measures are assessed at three timepoints across the study: a baseline questionnaire is completed prior to participants receiving access to the web-based program, a postprogram questionnaire at the conclusion of the web-based program access (2 months after baseline), and a follow-up questionnaire 4 months later (6 months after baseline). Figure 1 shows a flowchart of the study design and the participant numbers.

An RCT design was chosen for this trial to accurately compare outcomes for the 2 modes of delivery of the web-based *Back on Track* program, either self-directed or supported. By comparing outcomes for participants in the 2 groups, we will be able to determine whether the supported approach provides benefits over and above the self-directed use of the web-based *Back on Track* program. The result will then inform the optimal form of delivery of the *Back on Track* program for future rollout to people with CHD across Australia.

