### Intervention

#### Back on Track Program

The *Back on Track* program begins with a goal-setting module, followed by 4 self-selected modules relating to (1) healthy eating, (2) physical activity and reduced sitting, (3) smoking cessation, and (4) cardiac blues and depression. Participants in both the self-directed and supported arms are asked to complete modules relevant to them, in their own time and in any order over the course of 2 months. Within each module, participants undertake exercises that enable them to review situations in their lives, and using concepts from CBT, to identify, challenge, and change the unhelpful thoughts and beliefs associated with risk factors and negative emotions. Participants are prompted to develop action plans and coping plans for implementing practical health behaviors, including goal-setting, and identifying motivators for change, resources, barriers, rewards, and relapse prevention strategies. Other activities include using strategies to increase self-efficacy, including stories of role models, and exploring ratings of importance of and confidence to undertake behavior change.

The behavioral recommendations included in the modules (eg, healthy eating, physical activity, and smoking cessation) are all based on the current National Heart Foundation of Australia (NHFA) guidelines [52]. Although not being the central focus of the *Back on Track* program, it is important to present, up-to-date, relevant information on these guidelines and recommendations. This can help participants with aspects of their self-management, including goal-setting. Figures 2 and 3 show screenshots of various aspects of the web-based *Back on Track* modules.

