### Data Analysis

In evaluating outcomes, there will be two groups of participants based on the mode of delivery: “self-directed” and “supported.” All statistical analyses will be performed on an intention-to-treat (ITT) basis with *P*<.05. In the case that ITT produces a null finding, it is possible that this is due to participants in the supported group not participating in the additional telephone sessions (that is, not receiving the intended treatment). To test that hypothesis, we will then undertake treatment-received analysis (also called Per Protocol) whereby only those who received the treatment in accordance with the protocol are included. This will enable us to determine whether any differences were obtained between those who received the self-directed treatment and those who received the supported treatment. *P* values less than .05 will be considered significant for the primary outcome and those less than .01 will be considered significant for secondary outcomes. The effect of the intervention on the primary and secondary outcomes at 6 months will be assessed using analysis of covariance (ANCOVA) models that include the baseline value of the outcome as a covariate and the group assignment (self-directed versus supported) as a categorical variable. The treatment effect, its effect size (Hedge g), and 95% CIs for the treatment effect and within-group changes from baseline to 6 months will be calculated from the ANCOVA models. The sensitivity of the results to missing data will be evaluated using a data-based multiple imputation procedure.

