## Discussion

With cardiac event survivors at a heightened risk of a recurrent events and premature death, and with suboptimal attendance at center-based rehabilitation and secondary prevention programs, there is a need for innovative eHealth programs to support people in their behavioral and emotional self-management after an acute cardiac event. We anticipate that the *Back on Track* program will assist people in their recovery after an acute event and will represent a flexible, easily accessible, user-friendly, and effective adjunct to center-based programs. Our findings will enable us to quantify the behavioral and emotional improvements obtained and sustained for people with CHD who participate in the *Back on Track* program, while also comparing two methods of delivery: one fully self-directed and the other supported by a lifestyle counselor**.**

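### The first aim and hypothesis treat within-arm change as benefit of the web program, but both arms receive the program, so the trial cannot estimate its effect

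*Protocol article*

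**What the plan says.** All references are to the protocol article.

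- **Objectives, aim.** Two aims are given. The first reads "The aim of this study is to assess the benefits, in terms of behavioral and emotional well-being, of the web-based" program; the second is the added value of telephone support.
- **Objectives, hypotheses.** The first hypothesis is that "participants randomly allocated to each arm of the trial will show significant improvement in their behavioral and emotional well-being" from before to after the program, and it calls the persistence of that change a sustained benefit. The second is that the supported arm improves more than the self-directed arm.
- **Arms.** Under Back on Track Program: "Participants in both the self-directed and supported arms are asked to complete modules relevant to them". Under Study Design: "The supported arm involves the addition of 2 telephone sessions with a trained lifestyle counselor". No usual-care, wait-list or other arm without the program is described.
- **Purpose of randomisation.** Study Design says that comparing the groups will "determine whether the supported approach provides benefits over and above the self-directed use of the web-based" program.
- **Analysis.** Data Analysis plans an ANCOVA for the between-arm effect at 6 months. It adds that 95% CIs for the treatment effect and "within-group changes from baseline to 6 months will be calculated from the ANCOVA models". It names no within-arm significance test.
- **Expected conclusions.** The abstract's Conclusions anticipate that the program "represents an effective, flexible, and easily accessible adjunct to center-based rehabilitation programs". The Discussion says "Our findings will enable us to quantify the behavioral and emotional improvements obtained and sustained for people with CHD who participate" in the program, and likewise anticipates that it will be effective.

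**The concern.** The first aim is a causal question about the program, and the first hypothesis answers it with change from baseline in people who all receive the program. Such a change contains whatever would have happened anyway. Three sources of change can be read from the document itself: participants are within 12 months of an acute cardiac event; attendance at cardiac rehabilitation is recorded but is not an exclusion; and the same questionnaires are completed three times.

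The randomised contrast isolates the effect of adding two telephone calls. If both arms improve to the same degree, the design cannot tell a program that works with calls that add nothing from a program and calls that both do nothing. If neither arm improves, it cannot tell an inert program from one that held off a decline. No analysis of these data can resolve either case, and nowhere does the article say that within-arm change cannot be attributed to the program. At stake is how the first of the two stated aims will be answered in the results paper.

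**Working it through.** **1. The plan's own sample size.** Inputs from Sample Size and Power: standardised effect 0.55, 80% power, significance threshold .05 (taken as two-sided), attrition 12%.

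n per arm = 2 × (1.960 + 0.842)² / 0.55² = 51.9, so 52. Allowing for attrition: 52 / 0.88 = 59.1, so 60 per arm and 120 in total. The stated figure reproduces. It is a two-group calculation, so it serves the supported versus self-directed comparison only.

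**2. What each comparison identifies.** Let P be the program effect, T the added effect of the telephone sessions and D the change that would have occurred without either.

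- Self-directed arm, change from baseline: P + D
- Supported arm, change from baseline: P + T + D
- Difference between arms: T

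P never appears without D. An estimate of P would need an arm whose change is D alone, and there is none.

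**3. How often drift alone would look like improvement.** This is an illustration for continuous scores. Completers per arm: 60 × 0.88 = 52.8, about 53. Drift d (in SD units) and the baseline to follow-up correlation r are assumptions; the document gives neither. P is set to zero, and T is ignored or the arm is the self-directed one.

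The standardised change for a paired t-test is dz = d / √(2(1 − r)). With r = 0.5, √(2 × 0.5) = 1, so dz = d. With r = 0.7, √(2 × 0.3) = 0.775, so d = 0.3 gives dz = 0.387. The power of the two-sided paired t-test at that dz is the chance that an arm shows a significant change:

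| Drift d | r = 0.5, level .05 | r = 0.5, level .01 | r = 0.7, level .05 |
|---|---|---|---|
| 0 | 5% | 1% | 5% |
| 0.1 SD | 11% | 3% | 15% |
| 0.2 SD | 30% | 12% | 45% |
| 0.3 SD | 57% | 32% | 79% |
| 0.4 SD | 81% | 60% | 96% |

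Both levels are shown because Data Analysis sets .05 for the primary outcome and .01 for secondary outcomes.

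**4. Limits of the illustration.** The section on primary outcome measures compares proportions: PHQ-9 below 6, at least 150 minutes of activity per week, and DQT above 60%. A paired t-test on a score does not describe these, so the table does not apply to them. The argument in step 2 does, because it does not depend on the scale of the outcome.

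**The case against.** The case for leaving the text alone has real substance.

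- **The design is legitimate for its delivery question.** Comparing two modes of delivery needs no arm without the program, and Study Design states the purpose of randomisation correctly. This stands; the second hypothesis is not criticised.
- **A reader might infer that the sponsor has committed to declaring the program effective if an arm improves significantly.** The document does not say so. The statements about effectiveness in the abstract and the Discussion are introduced as anticipation, and quantifying improvements can be read descriptively. The problem lies in the aim and first hypothesis under Objectives, which do speak of assessing benefits and of significant improvement.
- **A reader might infer that spontaneous improvement is likely on every outcome.** The document does not support that. Its Background reports high rates of poor diet, inactivity and return to smoking in the year after an event, and says that early lifestyle changes seldom last. For diet and activity, drift could be nil or adverse, and within-arm change could then understate the program. Regression to the mean is also hard to argue from the text, since entry requires no threshold of depression, activity or diet.
- **Part of the remedy is already planned.** Within-group changes to 6 months come with 95% CIs and no named test. True, but an interval that excludes zero would be read as the significant improvement that the hypothesis calls for. What is missing is the limit on attribution.
- **Earlier evidence supports the program.** The randomised trial described in the Background tested the face-to-face group version. For the web version the article cites a pilot on acceptability and usefulness. Neither provides the missing comparator.

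**Conclusion.** The point holds as one of aim, hypothesis and attribution. The design gives no estimate of the web program's effect, and the first aim and hypothesis under Objectives are worded as if it did. This follows from the structure of the arms and rests on no assumed number.

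The size of the possible error is not known. For continuous scores at r = 0.5, the chance that an inert program shows a significant change in an arm runs from about 11% to 81% at .05, and from about 3% to 60% at .01, over assumed drift of 0.1 to 0.4 SD. The drift and the correlation are both assumptions, no such figure is offered for the proportion-based main outcomes, and the drift could run in the adverse direction. The randomised contrast, its ANCOVA and the sample size of 120 are untouched.

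**What to change.** 1. In Objectives, restate the first aim and first hypothesis as descriptive: within-arm change at 2 and 6 months, reported with 95% CIs of the kind Data Analysis already plans for 6 months, and not judged for significance.
2. State there that this change cannot be attributed to the program, naming natural course after the event, concurrent cardiac rehabilitation and repeat testing as alternative explanations that may act in either direction.
3. Confine the words benefit and effective to the supported versus self-directed contrast, described as the effect of adding two telephone sessions, in line with Study Design.
4. Add the same caveat to the anticipated statements on effectiveness in the abstract's Conclusions and in the Discussion.

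Recruitment has closed with 122 enrolled, so the change is one of wording and calls for no new arm, data or recalculation. The cost is that the sponsor gives up a claim about the program's effectiveness that this design cannot support.
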